### Statistical analysis

Characterising the natural history of severe early onset FGR (Aim 1) will involve descriptive statistical methods, including means for numerical variables and proportions for binary or categorical variables. An initial analysis is planned for the first 65 study participants to help refine the inclusion criteria for the EVERREST Clinical Trial.

The association between individual factors and outcome will be analysed using t tests and chi-squared tests, and non-parametric tests used if required (Mann–Whitney U tests and Fisher’s exact tests). Logistic regression modelling will be used to investigate whether individual and combinations of factors can be used to estimate poor outcome (primary endpoint). These factors include ultrasound findings, levels and ratios of angiogenic factors, and potential markers identified through the semi-targeted and proteomic approaches. Due to the relatively small sample size, a forward selection algorithm will be employed, and it is likely that each model will only sustain a maximum of two or three independent variables. Models will be tested for goodness of fit and discrimination using leave-one out cross validation and bootstrapping.

Survival analysis, including Cox proportional hazards regression, will be used to investigate the predictive value of individual and combined factors for the secondary outcome measure of time until the end of pregnancy.

An a priori sample size calculation is not provided, as there is currently no reliable data on expected means and standard deviations of candidate markers within such a cohort, and no data on whether and how these would differ by outcome. Within our current sample of 65, with 5 withdrawals and 18 poor outcomes, there is a ratio of good to poor outcomes of 2.33. This sample will give an 80% power to detect a standardised effect size of 1.0 to a significance level of 0.05 [36]. The potential for type 1 error, given the multiple comparisons, or type 2 error, given the small sample size, will be borne in mind when interpreting the study results.

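### The stated power, effect size, significance level and sample do not agree: 18 poor and 42 good outcomes give about 94% power for a standardised difference of 1.0, and 80% power at about 0.80

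*Protocol article*

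**What the plan says.** All the relevant text is in the Statistical analysis section of the protocol article. The authors first explain that no a priori sample size calculation is offered, because reliable means and standard deviations for the candidate markers are lacking. They then describe the sample in hand: "Within our current sample of 65, with 5 withdrawals and 18 poor outcomes, there is a ratio of good to poor outcomes of 2.33". From it they draw the one power statement in the article: "This sample will give an 80% power to detect a standardised effect size of 1.0 to a significance level of 0.05", with a literature reference for the calculation.

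The comparison to which this applies is described earlier in the same section: "The association between individual factors and outcome will be analysed using t tests and chi-squared tests, and non-parametric tests used if required". The non-parametric alternative named for numerical variables is the Mann-Whitney U test. Sidedness is not stated, and no adjustment is built into the 0.05. Multiplicity is dealt with in words: "The potential for type 1 error, given the multiple comparisons, or type 2 error, given the small sample size, will be borne in mind" when the results are interpreted.

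**The concern.** The sentence gives everything needed for a two-group power calculation: both group sizes, the effect size, the significance level and the test. It can therefore be checked, and the answer is well away from 80%.

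Because the article gives no a priori calculation, this sentence is the reader's only quantitative guide to the sensitivity of the marker comparisons under the third aim. The section also says that type 2 error will be kept in mind at interpretation. A reader doing that with the stated figure would judge the sample less sensitive, for one marker tested at 0.05, than it is.

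**Working it through.** **Inputs, all from the Statistical analysis section**

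- Evaluable women: 65 − 5 = 60.
- Poor outcomes: 18. Good outcomes: 60 − 18 = 42.
- Check on the groups: 42/18 = 2.33, the ratio stated. Leaving the withdrawals in would give 47/18 = 2.61. So the sample meant is 18 against 42.
- Standardised difference d = 1.0; significance level 0.05, taken as two-sided because sidedness is not stated; two-sample t test.

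**Power at d = 1.0**

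- Standard error of the standardised difference: √(1/18 + 1/42) = √0.07937 = 0.2817.
- Noncentrality: 1.0 / 0.2817 = 3.55, with 18 + 42 − 2 = 58 degrees of freedom.
- Normal approximation: Φ(3.55 − 1.96) = Φ(1.59) = 94.4%.
- Noncentral t: 93.7%.
- Simulation (40,000 data sets for the t tests, 10,000 for Mann-Whitney): 93.7% for the t test, 93.0% for Welch, 92.3% for Mann-Whitney.

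The stated 80% is not reproduced.

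**Effect detectable with 80% power**

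- Normal approximation: (1.960 + 0.842) × 0.2817 = 0.789.
- Noncentral t: 0.803.
- Mann-Whitney, by scaling the sample by its relative efficiency: 0.82 at efficiency 0.955 (normal data) and 0.87 at 0.864 (the worst case). Power at d = 1.0 is then 92.6% and 89.9%.

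**Sample needed for 80% power at d = 1.0 and ratio 2.33**

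- Normal approximation for the smaller group: (1.960 + 0.842)² × (1 + 18/42) = 7.85 × 1.429 = 11.2, so 12 poor and 28 good outcomes, 40 in all.
- Noncentral t with 12 against 28: 80.6%.

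**Other readings of the sample, d = 1.0 (noncentral t)**

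| Reading | Power |
|---|---|
| 18 vs 42, one-sided 0.05 | 96.9% |
| 18 vs 47 (withdrawals not removed) | 94.4% |
| 65 split at ratio 2.33 | 95.3% |
| 13 vs 47 (all withdrawals from the poor group; contradicts the 2.33) | 88.1% |
| 18 vs 18 (equal groups) | 83.0% |
| 18 vs 42, two-sided 0.01 | 80.8% |

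No reading of the stated sample at 0.05 comes within 2 points of 80%. The figure is reached only by changing an input that the text states: a significance level near 0.01, or about 12 against 28 evaluable samples.

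**The case against.** The strongest reply is that little hangs on the sentence. The authors say plainly that there is no a priori calculation. The sentence describes a sample already in hand in a cohort study, and the article does not use it to set recruitment, a stopping point or a threshold. The error also runs in the safe direction for the comparison it describes. All of this stands, and it makes the point minor.

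A second reply is that the basis of the calculation is not visible: the cited source is not at hand, and the authors may have used a stricter level or allowed for missing samples. That is possible, and it means the wrong element could be the significance level or the evaluable number rather than the power or effect size. It does not rescue the sentence, which says 0.05 and refers to the sample just described.

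Two stronger readings are tempting, and the document supports neither.

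- A reader might infer that a null result would exclude differences above 0.8. The detectable difference is not an exclusion limit. With a standard error near 0.28, the 95% interval extends about 0.56 either side, so a just non-significant estimate of 0.56 has an upper limit near 1.13. A null result rules out 0.8 only if the estimate is below about 0.24 (0.80 − 0.56).
- A reader might infer that the sentence overstates sensitivity across the whole marker panel, since the Sample analyses section lists 7 targeted and 92 semi-targeted analytes. The stated 0.05 is a per-test level and makes no panel-wide claim. The section already acknowledges multiple comparisons, and it adopts neither a Bonferroni correction nor a defined family of tests.

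**Conclusion.** The statement is wrong as written; severity minor. For 18 poor and 42 good outcomes at two-sided 0.05, power for a standardised difference of 1.0 is about 94%, some 14 percentage points above the stated 80%. Eighty percent power is reached at about 0.80 instead of 1.0, or roughly 0.82 to 0.87 with a Mann-Whitney test. The sentence understates what the sample can detect for one unadjusted marker.

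This rests on a two-sided test, a common standard deviation, and a marker value available for all 60 women. One-sided testing widens the gap. The working does not show which of the four figures is the mistaken one, only that they cannot all hold together. The validity of the study is not affected.

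**What to change.** Restate the sentence, for example:

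> With 18 poor and 42 good outcomes the sample gives 80% power (two-sided 0.05, single unadjusted comparison) to detect a standardised difference of about 0.80, and about 94% power for 1.0.

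If a stricter significance level (about 0.01) or fewer evaluable samples (about 12 against 28) was in fact assumed, keep the 80% and the 1.0 and state that assumption, so that power, effect size, significance level and sample agree. Either way, state the sidedness.

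The cost is one sentence of text. Design, recruitment and the planned analyses do not change.

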### Sample analyses

Three initial analysis strategies are planned for maternal blood samples taken at study enrolment:Targeted angiogenic and anti-angiogenic markers: soluble FMS-like tyrosine kinase 1 (sFlt-1) and placental growth factor (PlGF) will be measured using the Roche Elecsys® automated electrochemiluminescence assay, VEGF-A, VEGF-D, soluble VEGF receptor-2, soluble endoglin, and neuropilin 1 will be measured using R&D Systems enzyme-linked immunosorbent assays (ELISAs).Semi-targeted vascular markers: 92 serum analytes implicated in cardiovascular disease will be measured on the Olink ProSEEK platform, using DNA primer-tagged antibody pairs in a proximity extension assay to provide very sensitive (1 uL serum) and specific measurements.Non-targeted proteomic analysis: a mass spectrometry-based serum profiling approach will be employed for the discovery of potential new biomarkers. Serum samples will be pooled into good and poor outcome groups and subjected to an established proteomic profiling workflow involving immunodepletion of the 12 most abundant serum proteins, tryptic digestion, 6-plex tandem mass tagging (TMT), and two-dimensional liquid chromatography (high and low pH reversed-phase) linked to quantitative tandem mass spectrometry. Candidate selection from the combined dataset will be based on standard statistical tests of fold-change, MS data quality and known function. Selected candidates will be further verified in the individual discovery samples using commercial ELISAs.

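### Multiplicity across 99 named blood markers is handled by interpretation only; at 0.05, the only level given, about five nominal hits are expected even if none is prognostic

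*Protocol article*

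**What the plan says.** All references are to the protocol article.

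- **Markers (Sample analyses).** The targeted set is given in two parts: "soluble FMS-like tyrosine kinase 1 (sFlt-1) and placental growth factor (PlGF) will be measured" on one platform, and "VEGF-A, VEGF-D, soluble VEGF receptor-2, soluble endoglin, and neuropilin 1 will be measured using R&D Systems enzyme-linked immunosorbent assays". The semi-targeted set is a panel: "92 serum analytes implicated in cardiovascular disease will be measured on the Olink ProSEEK platform". A mass-spectrometry screen of pooled serum follows, with no stated number of proteins; its selected candidates are re-measured by ELISA in the discovery samples.
- **Tests (Statistical analysis).** "The association between individual factors and outcome will be analysed using t tests and chi-squared tests", with non-parametric alternatives if needed.
- **Route into the models (Statistical analysis).** Logistic regression for the primary endpoint draws on a wide pool: "These factors include ultrasound findings, levels and ratios of angiogenic factors, and potential markers identified through the semi-targeted and proteomic approaches". Forward selection is used, each model is expected to carry at most two or three variables, and models are checked by leave-one-out cross-validation and bootstrapping.
- **Level (Statistical analysis).** 0.05 appears once: "This sample will give an 80% power to detect a standardised effect size of 1.0 to a significance level of 0.05".
- **Multiplicity (Statistical analysis).** "The potential for type 1 error, given the multiple comparisons, or type 2 error, given the small sample size, will be borne in mind" when the results are interpreted.

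**The concern.** The article does not leave multiplicity open. It states an approach, and that approach changes no threshold, ranking or list of declared markers. With about a hundred markers compared by outcome, some nominally significant results are close to certain whether or not any marker is prognostic. A reader of the results would have no stated error rate for an analyte called a marker.

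Identifying prognostic markers is one of the three stated aims and has its own primary endpoint. The Discussion says markers may help refine eligibility for later-phase trials and expects the findings to improve counselling and guide management. Chance findings could therefore reach the models for fetal or neonatal death and then later decisions.

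**Working it through.** **Inputs**

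- Targeted markers: sFlt-1 and PlGF (2), plus VEGF-A, VEGF-D, soluble VEGF receptor-2, soluble endoglin and neuropilin 1 (5), so 7 (Sample analyses).
- Olink panel: 92 (Sample analyses). Total 7 + 92 = 99.
- Level: 0.05, the only one given (Statistical analysis). Its use as the marker threshold is an assumption.
- Group sizes: "Within our current sample of 65, with 5 withdrawals and 18 poor outcomes, there is a ratio of good to poor outcomes of 2.33". So 65 - 5 = 60 analysable, 18 poor and 60 - 18 = 42 good; 42/18 = 2.33, as stated.

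**1. The plan's own power figure.** With 18 v 42, effect 1.0 and two-sided 0.05, the normal approximation gives power = Φ(1/√(1/18 + 1/42) - 1.96) = 94.4%. The t distribution gives 93.7%, and Mann-Whitney about 90 to 93%. The stated 80% is not reproduced. It would need a level of about 0.007 (normal) to 0.009 (t), which the article does not mention. This is a separate matter, but it matters here because this sentence is the only source of the 0.05.

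**2. Expected false hits if no marker is prognostic** (number of tests x 0.05)

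| Set | Tests | Expected | P(at least one), if independent |
|---|---|---|---|
| Targeted | 7 | 0.35 | 1 - 0.95^7 = 30.2% |
| Olink | 92 | 4.6 | 1 - 0.95^92 = 99.1% |
| Both | 99 | 4.95 | 1 - 0.95^99 = 99.4% |

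Under independence the 95% range for 99 tests is 1 to 10 hits. Correlation between markers leaves the expected count unchanged, widens the spread and lowers the chance of at least one.

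**3. If some markers are real.** The number is not in the document, so a range is assumed, with real markers detected at the article's 80%.

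| Real markers | False hits | True hits | False share of hits |
|---|---|---|---|
| 5 | 94 x 0.05 = 4.70 | 5 x 0.8 = 4 | 4.70/8.70 = 54% |
| 10 | 89 x 0.05 = 4.45 | 8 | 4.45/12.45 = 36% |
| 20 | 79 x 0.05 = 3.95 | 16 | 3.95/19.95 = 20% |

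Ratios, ultrasound findings, proteomic candidates and the second endpoint are not counted.

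**4. Whether the model checks compensate.** In a simulation of 99 independent null markers with 18 poor and 42 good outcomes (300 runs), the two markers with the largest t statistics went into a logistic model. This simplifies forward selection. About 5 markers per run were nominally significant. True discrimination is 0.5. When selection was done once on all the data, the leave-one-out AUC averaged 0.72 (5th to 95th percentile 0.65 to 0.79). When selection was repeated in each fold, it averaged 0.47. The protection therefore depends on a step the article does not state.

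**5. Cost of control.** The strictest Benjamini-Hochberg step for 92 tests is 0.05/92 = 0.00054. At that level the effect detectable with 80% power (18 v 42) is 1.21 (normal) or 1.28 (t), against 0.79 or 0.80 at 0.05. Benjamini-Hochberg lies between these, nearer the milder end when more analytes are truly associated.

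**The case against.** The strongest reply has four parts.

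- **The threshold is inferred.** A reader might infer that the plan declares any marker with p < 0.05. It does not say so: 0.05 stands only in the power sentence, and that sentence does not reproduce at 0.05. This objection stands, so the count of about five is conditional. What does not depend on it is that the stated approach to multiplicity is interpretive only.
- **There are safeguards.** A reader might also conclude that nothing in the plan separates chance findings from real ones. That goes too far. Forward selection, the small model size, cross-validation, bootstrapping, and ELISA verification of proteomic candidates all bear on the matter. They fall short because the first four act on models and not on which individual markers are declared, and the ELISA step re-measures the same women and covers only the proteomic arm.
- **Chance hits need not enter a model.** This stands. They become candidates, and with two or three variables per model most of about five cannot enter any one model.
- **This is discovery work.** The analyses are called initial, both error types are openly acknowledged, and with 18 events strict control costs power. This argues against familywise control over all 99 markers: at 0.05/99, power for an effect of 1.0 falls to about 46% (t) or 53% (normal). It is not an argument against a false discovery rate, which suits an exploratory panel.

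That the detail might belong in an analysis plan is not an answer, because the article states its approach.

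**Conclusion.** The point holds in conditional form. If the 7 targeted and 92 Olink analytes are tested at 0.05, about 5 of 99 (4.6 of 92) nominal hits are expected with no prognostic marker at all, and still about 4 to 5 if up to 20 are real. The expected count needs no independence assumption; the 99% probabilities do. The simulated AUC inflation rests on independent null markers and a simplified selection step, and applies only if selection is not repeated in each fold, on which the article is silent.

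The documents do not support saying that 0.05 is the plan's selection rule, that the plan has no safeguards, or that false hits are bound to enter the models. The point is worth correcting, because the remedy is cheap and the markers are meant to inform later trials. It does not undermine the cohort or its descriptive aim.

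**What to change.** In Statistical analysis, replace the sentence on type 1 error, as far as it concerns the Olink panel, with text such as:

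> The 92 analytes will be reported with Benjamini-Hochberg adjusted p-values, and only those at a false discovery rate of 5% will be described as identified markers; all analytes will be reported with estimates and 95% confidence intervals. The seven pre-specified angiogenic markers are reported as a separate family, with the number of tests stated. Any cross-validation or bootstrap will repeat the marker-selection step within each fold or resample.

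Two limits on the change:

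- Univariate significance should not be a hard gate into the multivariable models. The article sets out to study combinations and ratios, and a gate could drop markers that are useful only jointly.
- The same rule should not be imposed on the proteomic screen. It runs on pooled serum with six-plex tagging, so per-protein replication is limited and the number of plexes is not stated.

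The cost is a short paragraph, some extra computation for the resampling, and no new data or participants. The real downside is that fewer analytes will be declared as markers and power per Olink analyte is lower, at worst that of the strictest step shown above.

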## Discussion

Developing novel maternal and fetal therapies raises many challenges [37]. By characterising the natural history of severe early onset FGR the EVERREST Prospective study will make it possible to assess the safety and efficacy of maternal Ad.VEGF gene therapy in an early phase clinical trial. The identification of prognostic markers may also help refine the eligibility criteria for later phase clinical trials, improving the chance of successful translation into the clinic. The natural history data will also be available for comparison with other novel therapies that may be in development [2].

Establishing this study within the context of a pan-European collaboration has provided both challenges and benefits. Development of the study protocol and SOPs has highlighted the variation in practice that exists between clinical fetal medicine units. Routine clinical practice in the four study sites uses different methods of measuring fetal biometry, different formulae for EFW, and different reference ranges for EFW and Doppler measurements. These have been harmonised for the EVERREST Prospective Study, providing us with the basis to move forwards for the EVERREST Clinical Trial. Through establishing the ultrasound validation system we have also addressed the potential for variation in practice in a multicentre study.

Defining the eligibility criteria was complicated by the considerable heterogeneity in the way the term FGR is used and defined. An EFW below the third centile has been chosen as the inclusion criteria for the EVERREST Prospective Study in order to identify the smallest fetuses, at the highest risk of adverse perinatal outcome [17]. This is consistent with the recent Delphi consensus on the definition of early placental FGR [38]. An upper limit of 600 g and 26+6 weeks of gestation was included because Consortium members considered that above these parameters, delivery would be a more appropriate option than participation in the EVERREST Clinical Trial. The inclusion criteria do not include any Doppler ultrasound measurements, meaning that there is the potential for inclusion of pregnancies where the fetus is constitutionally small. This was a deliberate decision in order to avoid initially excluding women who subsequently manifested signs of placental insufficiency. More restrictive eligibility criteria are planned for the EVERREST Clinical Trial, and outcomes will be compared with women from prospective study who would have met these more stringent criteria.

An important feature of the EVERREST Prospective Study is the detailed maternal, fetal, and infant data that are being collected. The outcomes to be recorded were initially developed by pooling variables collected in other obstetric and neonatal studies across the four centres. Shortly after the launch of the study COLAB published their minimum and optimum data sets for studies on pre-eclampsia [28]. Many of these variables are applicable to all studies in pregnancy, and given the overlap between pre-eclampsia and FGR they are particularly relevant to the EVERREST Prospective Study. We therefore expanded the data collection to include the majority of their optimal data set. COLAB will shortly be launching a database incorporating their recommended data sets, which will be a valuable resource for future pregnancy studies.

The EVERREST Prospective Study has been designed to support the development and conduct of the EVERREST Clinical Trial, but we believe that its findings will have wider applications. By providing outcome data and prognostic markers for a severe early onset subset of FGR, this study is likely to improve future patient counselling and guide clinician’s management. The bio-bank of comprehensively phenotyped samples will also support future research into the biological mechanisms underlying FGR, and hopefully identify novel targets for future therapies.

## Abbreviations

Ad.VEGF: Adenoviral vector vascular endothelial growth factor gene therapy
COLAB: Global Pregnancy CoLaboratory
DNA: Deoxyribonucleic acid
EFW: Estimated fetal weight
ELISA: Enzyme-linked immunosorbent assay
EPDS: Edinburgh postnatal depression scale
EVERREST: Does vascular endothelial growth factor gene therapy safely improve outcome in severe early-onset fetal growth restriction?
FGR: Fetal growth restriction
GMFCS: Gross motor function classification system
HIV: Human immunodeficiency virus
ISUOG: International society of ultrasound in obstetrics and gynecology
MACS: Manual ability classification system
MVM: Maternal vascular malperfusion
PI: Pulsatility index
PlGF: Placental growth factor
PPQ: Perinatal posttraumatic stress disorder questionnaire
RNA: Ribonucleic acid
ROC: Receiver operating characteristic
RRPQ: Reactions to research participation questionnaire
sFlt-1: Soluble FMS-like tyrosine kinase 1
SOP: Standard operating procedure
STAI: State-trait anxiety inventory
TAMEAN: Time averaged mean
TMT: Tandem mass tagging
VEGF: Vascular endothelial growth factor
